#### Primary outcomes

There will be two primary outcome measures: individual fruit (excluding juices) and vegetable (including potatoes and legumes) consumption (measured as serves consumed/day). Changes in consumption of F&V servings/day, will be calculated as the mean difference, between baseline (pre-) and post-intervention (with 95% Confidence Intervals [CI]). A standard serve of fruit is approximately 150 g (approx. 5.3 oz) and a standard serve of vegetables is approximately 75 g (approx. 2.6 oz) [53].

The first two questions, that relate to children’s F&V consumption, have been chosen from the food frequency questionnaire (FFQ) used in the *Many Rivers Diabetes Prevention Project* [54]. This FFQ has been used among Australian children aged 10–12 years, and has been assessed for and found to have, criterion/concurrent/predictive validity and reliability [55].

#### Secondary outcomes

Secondary outcomes will include nutrition consumption and food literacy constructs such as: nutrition knowledge, food preparation and cooking (skills, self-efficacy and behaviour), food waste (knowledge and behaviour), and food production (knowledge). All outcomes will be calculated as differences between baseline (pre-) and post-intervention.

##### Nutrition (F&V consumption, variety and knowledge)

The proportion of children consuming the recommended two serves of fruit/day will be calculated. According to the Australian Bureau of Statistics, only 6.3% of children meet their recommended intake of five vegetables/day, with an average intake of only two serves/day [7]. Therefore, a more conservative level of two serves/day will be used to assess changes in proportion of students consuming vegetables. For analyses involving proportions, intakes of F&V will be dichotomized to 0–1 serves/day verses ≥2 serves/day. These outcomes will be calculated using the same two questions used for the primary outcomes.

Vegetable variety (number of different types of vegetables consumed yesterday), fruit variety (number of different types of fruits consumed yesterday), and the mean number of the variety of the different F&V consumed, will be calculated (with 95% CI), as well as the proportion (in percentages %) of students consuming these F&V. To capture variety of F&V eaten by children, two questions were taken from the *Modified Child Nutrition Questionnaire* (MCNQ) [56], which was designed to assess dietary patterns in Australian children aged 9–13 years, and has face/content validity, criterion/concurrent/predictive validity and reliability [55]. However, there has been an addition of ‘other’ under the list of fruits and vegetables listed in these questions, with the opportunity to state which ‘other’ F&V children consume. This was used in order to capture the different varieties of F&V consumed by children from culturally and linguistically diverse (CALD) backgrounds. The inclusion of questions that are sensitive to populations that are CALD, was one of the lessons learnt from the FEAST pilot study, given the schools that participated in the pilot, had a high percentage of students that were from diverse ethnic backgrounds, as well as a small percentage of students from Indigenous backgrounds.

Nutrition knowledge will be calculated as the proportion (%) of students reporting knowing the recommended intakes of fruit and vegetable serves/day. Questions for this outcome were also taken from the MCNQ [56], however the multiple-choice responses were modified and simplified to include only specific servings/day with the exclusion of responses that included servings/week.

##### Cooking (skills, self-efficacy and behaviour)

The proportion (%) of students reporting the following, will be calculated: the ability to prepare food (i.e. fruit snack, vegetable snack, salad); help family make a meal; measure ingredients; cut food; follow a recipe; and the number of times/week they help their family cook dinner at home. Also, the mean score of the number of ‘yes’ responses to these questions will be calculated out of a possible seven ‘yes’ responses, and compared between baseline and post-intervention. The seven questions to assess these outcomes were taken from the survey used in the *Cooking with Kids* program and have been validity-tested for self-efficacy among children aged 9–11 years [57]. The question that measures behaviour change (i.e. help their family cook dinner at home), was taken from the *Experiential Cooking and Nutrition Education Program*, that was designed to increase cooking self-efficacy and vegetable consumption in children in Grades 3–8 [58] however, it has not been tested for validity and/or reliability.

##### Food waste (knowledge and behaviour)

The proportion (%) of students reporting the amount of their school lunch consumed; why they consumed that much; what they do with the food they do not eat; as well as why and how they dispose the food they do not eat, will be calculated. The four questions for this outcome were modified from one published study investigating food waste behaviours among children in Western Australian upper primary and lower secondary schools (Grades 5–8) [59]. However, this survey has not been validated to date. Most validated measures for school mealtime waste involve observations and assessments of food plate waste, such as digital photography [60, 61]. This is not an option in this study, as Australian primary schools do not have national school lunch programs as they do in the US [60] and UK [62], instead Australian children are more likely to bring their lunch from home [63] or purchase it from the school canteen [64]. Also, a food waste audit was not feasible as a more intensive program of research would be required and is beyond the time and resources available for this trial.

The proportion (%) of students reporting their understanding of the impact of food waste on the environment; whether they eat ‘imperfect’ F&V; and whether they are willing to eat or use ‘imperfect’ bananas in a recipe, will be calculated. Also, two open-ended questions will be asked of the students: what ‘food waste’ means to them and how they think food waste impacts the environment. The questions for these outcomes were specifically developed for the FEAST program and were aligned with food waste lessons.

##### Food production (knowledge)

Understanding of the ‘farm to plate’ concept, will be calculated as the proportion (%) of students reporting the correct sequence of a strawberry’s journey from farm to plate. The question for this outcome was also specifically developed for the FEAST program and was aligned with the food production lesson.

A combination of dichotomous (yes/no) responses, multiple choice options, Likert scale questions and short sentence answers, make up the surveys. Each survey question has been written in simple language and several questions are accompanied with an illustration to enhance understanding, such as F&V serving sizes. In addition, two posters with the images of the F&V that appear in the questions relating to F&V variety, will be provided to the teachers to display them in the classroom, so that students have additional visual aids to assist them with the F&V questions. For ease of use, the survey was created within the electronic data capture system called REDCap, which will entail the self-reported pre- and post-intervention surveys, which should take between 20 and 30 min to complete. Children aged 10–12 years of age, are capable of self-reporting constructs like these [65].

In order to enhance successful completion of the FEAST survey, the following evidence-based recommendations have been included: short completion time [66]; training of teachers to explain questions and monitor children [65]; use of visual prompts [65, 67]; use of technology, such as online surveys [68]; and reduced retention interval, by asking children to recall what they ate in the previous 24 h [69].

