OzHarvest provides training, resources and support to teachers to deliver a recommended 1.5-h lesson/week, for a 10-week unit of inquiry (incorporating 10 theory and six practical activities) within the classroom setting. The FEAST program has been integrated with lessons mapped to the Australian Curriculum, embracing Grade 5–6 key learning areas (KLAs) i.e. English [44]; STEM (Science, Technology, Engineering, and Mathematics) curriculum [45]; general capabilities (Literacy, Numeracy, Information and Communication Technologies, Critical and Creative Thinking, Personal and Social Capability and Intercultural Understanding) [46]; and the cross-curriculum priority of sustainability [47]. FEAST has been aligned with the Australian Dietary Guidelines and state/territory-based healthy eating strategies [1], with all recipes including either fruits and/or vegetables (which are also the two most wasted food groups [48]). The program includes a range of educational resources designed to assist in the delivery of the theory and practical components as outlined in Additional file 2 [49]. The lesson plan topics are outlined in Additional file 3 and the practical guide components are outlined in Additional file 4.

Grade 5–6 classroom teachers from the schools that volunteer to participate in the FEAST program, will be invited for a training workshop at OzHarvest offices. A Professional Learning Program will be delivered over six hours of face-to-face training. During the training day, two FEAST education team members will train the teachers in food preparation and cooking skills (making the hot and cold recipes designed for the FEAST program). To assist the teachers and students during the class practical components, teachers will be provided with instructions and resources to seek volunteers throughout the school community such as parents/caregivers, grandparents, and/or school staff etc. Trained volunteers will also be available through OzHarvest, to assist during the practical components. It is recommended that the teachers organize at least one adult per five students, for each of the practical sessions, in addition to themselves.

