Strategies to support data collection involve: training the teachers to use the REDcap platform (used for data collection) and to familiarise them with survey questions; training OzHarvest volunteers to assist in data collection; a video by [name] (OzHarvest CEO and founder) thanking students and teachers for participating in the FEAST program and encouraging them to complete the post-FEAST surveys; and two email reminders to teachers to complete surveys. The primary investigator (PI) will also assist during teacher training sessions and she or a trained OzHarvest volunteer will be available to assist teachers in data collection, pre- and post-FEAST (subject to COVID19 regulations). Every school that participates in this trial, will be rewarded with a gift voucher, worth $100.00 AUD, if the students complete both pre- and post-FEAST surveys and the teachers complete the program evaluation survey. Additionally, schools will be eligible to win one of five prizes (worth $100.00 AUD) for the best School Cookbook produced. The cookbooks will be judged by the FEAST education and research teams.

OzHarvest has secured funding for the FEAST program from governmental, corporate and philanthropic sponsors, to cover the costs of the program, including teacher training, curriculum package and cooking equipment. This is offered to schools with an Index of Community Socio-Educational Advantage (ICSEA) below the average ICSEA value of 1000 and to schools that are in regional or remote Australia, that are interested in participating in the program. The ICSEA information is published on *MySchool* website [50]. However, depending on the funding offer some schools will need to fund the purchase of the food/ingredients required for the cooking activities or ask for support from local businesses. The estimated cost of the food required for 30 students to undertake the six cooking activities is $300.00 AUD. Schools with an ICSEA above 1000, will need to cover the costs of the entire FEAST program for themselves (estimated to cost $4000.00 AUD).

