### Data collection methods

The class teachers participating in the FEAST trial, will receive a URL link to access student surveys, on the REDcap platform, in the last week of the school term preceding implementation. The teacher will then email this link to his/her entire class in week one of the school term, that FEAST will be implemented. At the end of the school term, a second URL link will be issued to the class teachers to access the post-FEAST survey. The teachers will set up a time for all students in their class to complete the pre-FEAST survey prior to starting the program (T1) and the post-FEAST surveys on program completion (T2). Schools acting as the wait-list controls will also complete the surveys at the same time as intervention schools (i.e. at T1 and T2). The PI (FK) and/or OzHarvest volunteers will assist the teachers in data collection (subject to COVID19 regulations).

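### Unblinded teachers who deliver FEAST know the survey items, are trained to explain them and run the survey sessions, so help at follow-up could inflate secondary knowledge outcomes, most clearly the farm-to-plate item

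*Protocol article*

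**What the plan says.** All references are to the protocol article.

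- **Who delivers.** Under Intervention: "OzHarvest provides training, resources and support to teachers to deliver a recommended 1.5-h lesson/week, for a 10-week unit of inquiry". Under Blinding (masking), the article states that neither students nor teachers can be blinded.
- **What teachers know.** The strategies to support data collection, also under Intervention, include "training the teachers to use the REDcap platform (used for data collection) and to familiarise them with survey questions".
- **What teachers do at the survey.** The end of the section Food production (knowledge) lists "training of teachers to explain questions and monitor children [65" among the measures to help pupils complete the survey. Data collection methods adds: "The teachers will set up a time for all students in their class to complete the pre-FEAST survey". It gives teachers the same task for the post-program survey. The investigator or OzHarvest volunteers may assist, subject to COVID19 rules.
- **The farm-to-plate item.** The outcome is the "proportion (%) of students reporting the correct sequence of a strawberry’s journey from farm to plate". On its origin: "The question for this outcome was also specifically developed for the FEAST program and was aligned with the food production lesson".
- **Recommended serves.** "Nutrition knowledge will be calculated as the proportion (%) of students reporting knowing the recommended intakes of fruit and vegetable serves/day". These questions come from an existing child nutrition questionnaire, with simplified response options.
- **Food-waste items.** "The questions for these outcomes were specifically developed for the FEAST program and were aligned with food waste lessons". The text states no correct-answer scoring for them; the response options are in an additional file that is not shown.
- **Safeguard.** The Discussion says pupils will be told that the survey is not a test and has no right or wrong answers. This is offered against social desirability.

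**The concern.** The person who delivers the intervention also has a hand in measuring its effect. By the second survey a FEAST teacher has seen the items, has taught a lesson that one of them was written to match, and is in the room with a general brief to explain questions. A well-meant explanation of an item with a right answer can give that answer away. A control teacher has not taught the lesson and has less reason to steer pupils towards it.

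At stake is the reading of the secondary knowledge outcomes. A higher proportion correct in the FEAST arm could reflect learning, help on the day or rehearsal of a known item, and the trial data could not separate these. Blinding the biostatistician does not touch the problem, and adjusting for baseline does not remove help that differs between the two surveys.

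**Working it through.** **1. The passages side by side.**

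| Item | Right answer stated? | Written to match a FEAST lesson? |
|---|---|---|
| Farm-to-plate sequence | Yes | Yes |
| Recommended fruit and vegetable serves | Yes, by its nature | No, existing questionnaire |
| Food-waste understanding, imperfect produce, open questions | Not stated | Yes |
| Fruit and vegetable serves per day (primary) | No, reported intake | No, existing questionnaire |

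Only the first row has both features. The second row is exposed to help on the day but was not built around the lessons.

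**2. Do the stated protections reach this route?**
- The message to pupils about right or wrong answers does not fit an item scored for a correct sequence, and it places no limit on the teacher.
- Baseline adjustment (Statistical analysis) absorbs part of a teacher's constant habit of helping. It does not absorb extra help at follow-up.
- The additional helpers are conditional, and the volunteers come from the organisation that designed the program.

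**3. Size: illustration only.** The article gives no power or expected percentage for any knowledge outcome. Its only power figures, 90% for vegetables and 97% for fruit, serve here to check the design inputs.

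Inputs from Sample size: 10 schools per arm; 50 students, read as per school; CV 0.436; ICC 0.04; 20% loss, leaving 40 per school; correlation 0.5; SDs 1.3 and 1.1; effect 0.5; two-sided alpha 0.025.
- Design effect = 1 + ((1 + 0.436²) × 40 − 1) × 0.04 = 2.86. Effective pupils per arm = 400 / 2.86 = about 140.
- Vegetables: SE = 1.3 × √(1 − 0.5²) × √(2/139.7) = 0.135. Noncentral t with 18 df gives 88.6%.
- Fruit: SE = 1.1 × √(1 − 0.5²) × √(2/139.7) = 0.114, giving 96.6%.

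Both lie within 2 points of the stated figures, so the inputs are usable.

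Now let p be the share correct unaided, and c the share of FEAST pupils who would have answered wrongly but are led to the right answer. Assume no true learning and no extra help in controls.
- False difference = c × (1 − p).
- SE = √(2 × p(1 − p) × 2.86 / 400), which is 0.055 at p = 0.3 or 0.7 and 0.060 at p = 0.5.
- Chance of p < 0.05, two-sided, from the noncentral t with 18 df:

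| p | c = 5% | c = 10% | c = 20% |
|---|---|---|---|
| 0.3 | 3.5 points, 9% | 7 points, 23% | 14 points, 67% |
| 0.5 | 2.5 points, 7% | 5 points, 12% | 10 points, 35% |
| 0.7 | 1.5 points, 6% | 3 points, 8% | 6 points, 18% |

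The values of p and c, the use of ICC 0.04 for a binary item, the 5% level and the absence of a gain from baseline adjustment are assumptions. The table runs from negligible to serious, and the documents do not say where the trial would fall.

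**The case against.** The strongest reply is that explaining questions to 10–12-year-olds naturally means clarifying the wording, and that detailed administration rules belong in training material that a journal article does not print. This partly stands. A reader might infer that teachers will supply answers, but nothing in the article says so. The point is therefore not that a rule is missing. The article adopts explanation by the delivering teacher as a procedure, and in open terms.

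A reader might also infer that all three knowledge domains are scored on lesson-matched right answers. The article does not support that: it shows both features only for the farm-to-plate item.

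A reader might infer, too, that only the FEAST arm can gain. Control classes take the same surveys at the same times, and neither the familiarisation nor the explaining is restricted to FEAST-arm teachers, so help on the day may occur in both arms. What is more specific to FEAST is follow-up help from someone who has just taught the matching content, and teaching to a known item during the term.

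Finally, testing taught content is legitimate for an immediate knowledge outcome, and teaching the farm-to-plate sequence is part of the program. That stands. Alignment alone is no fault; the weakness is alignment combined with an unblinded deliverer who knows the item and may explain it.

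**Conclusion.** The point holds in a limited form. The adopted procedure lets unblinded delivering teachers influence how secondary knowledge outcomes are measured at follow-up. The farm-to-plate item is the clear case and the recommended-serves items a lesser one. The size of any bias cannot be derived from the documents. On the assumptions shown, the false difference runs from 1.5 to 14 percentage points, and the chance of a falsely significant result from 6% to 67%. These figures illustrate possible sizes and do not predict what will happen.

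The primary fruit and vegetable intake outcomes and their power are not the target. The change is worth making because it is cheap and because no later analysis can separate the explanations.

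**What to change.** Replace the open-ended instruction to explain questions with one fixed script, used by teachers and any helpers in both arms at both surveys. It should limit help to log-in, reading aloud, clarifying wording and pointing to the serve-size pictures. It should also tell them not to discuss or hint at the content of items with a correct answer.

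Leaving those items out of teacher training would not hide them: teachers receive the survey link in the term before and run the baseline survey before the lessons begin. The script therefore addresses help on the day but not teaching to the item. For the latter, the report should state that gains on lesson-aligned items may partly reflect it.

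The cost is about a page of instructions and a small edit to the training session. The downside is a few more blank or uncertain answers, possibly more among pupils who speak another language at home.

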#### Process evaluation outcomes

The RE-AIM framework (Reach, Efficacy, Adoption, Implementation and Maintenance) [70] has been adopted to guide the process evaluation along with the inclusion of two other parameters. The evaluation of the ‘efficacy’ component (or in this real-world trial ‘effectiveness’) has been described above, under ‘outcomes’. This process evaluation will assess program: reach (to students and teachers); adoption (by schools); implementation (training of teachers, adherence by students and teachers; barriers and facilitators to implementation); maintenance (intention by students and teachers); satisfaction (of students and teachers); and perceived benefits (by teachers for their students). (Refer to Additional files 6 and 7 for full details of all questions and response options for the student and teacher process evaluation surveys, respectively).

##### Reach of program (teacher and student)

Reach may be defined as the proportion of participants who are eligible but did not participate in some or all of the intervention compared to those who participated in all of the intervention [70]. To evaluate the FEAST program’s reach, the post-intervention teacher survey includes questions that ask teachers: how many students in their class and how many of their students participated in the FEAST program.

##### Adoption of program

Adoption refers to the proportion of settings that adopt a given program [70]. This can be assessed by involving the program creators and educators of the FEAST program (i.e. OzHarvest) and asking them to provide the numbers of schools approached and the number of schools that have adopted the program.

##### Implementation (training of teachers, adherence by students and teachers; barriers and facilitators)

Implementation can be defined as the extent to which a program/intervention was delivered as intended, which can be examined at the individual-level and program-level [70]. To monitor adherence/fidelity at the program-level, and to investigate whether teachers delivered the intervention as intended, the post-intervention teacher survey includes questions that ask teachers: what type of training they undertook (face-to-face vs online vs no training); if they implemented the program alone or with another teacher; how many of their students participated in the FEAST program; how many FEAST lessons were conducted; how many cooking sessions were conducted; and if the class created a school cookbook. To monitor adherence at the individual (student level) there is a question embedded within the student post-intervention survey, asking students whether they participated in the cooking activities.

To evaluate whether teachers received all of the resources required to implement the program, embedded within the question to rate the effectiveness of the resources, teachers will also need to ‘tick’ the resources they did not receive.

To gauge potential barriers to implementation, teachers will be asked: if there were any classroom, school or external barriers that impeded students undertaking the FEAST program; whether cost was a barrier to delivering the program; and whether finding volunteers to help with the practical components was an issue.

To gauge potential facilitators, teachers will be asked open-ended questions such as: to describe their favourite aspect of the program; which aspects of the program they thought had the greatest impact on their students; whether they would continue implementing the program and why/why not. Lastly, they will be asked whether they have any feedback, and if they have any suggestions as to how OzHarvest could modify the program in the future.

